### Sample

The project is currently in progress. The cohort will comprise all consumers admitted to the three MSAMHS CCUs (Bayside, Coorparoo and Logan) between December 2014 and December 2017 who provide informed consent to participate. Baseline and follow-up data will be sourced from administrative datasets for the 12-month period prior to and following CCU admission and discharge respectively.

As the study takes a naturalistic observational design, the only defined inclusion criteria is acceptance for a trial of CCU based rehabilitation care. Each CCU provides a six-week assessment period to establish suitability for engagement under the model of service. Given this, consumers who are discharged prior to the conclusion of this assessment period will be excluded from the study. This exclusion criterion assists in ensuring that included participants are aligned with the model of service. This reflects a modified intention-to-treat approach [34], as participants will be included regardless of their mode of exit from the CCU (planned/unplanned (CCU initiated)/unplanned (consumer initiated).

Based on anticipated service throughput, with a median length of stay at the Coorparoo CCU of 0.9 years (inter-quartile range 0.50-1.8 years) at a point estimate in 2013, and assuming a 70 % response rate, it was expected that at least 60 consumers from the integrated staffing model and 40 from the clinical staffing model would agree to participate over the study period. This minimum sample likely reflects an under-estimate given 37 unique admissions occurred to the Coorparoo CCU in the 12-month period from July 2012. Additionally, since the opening of the Bayside and Logan CCUs 50 of the 63 consumers admitted across all three sites met the inclusion criteria (79.4 %) and 42 (84.0 %) of eligible consumers provided consent to participate.

The adequacy of the estimated minimum sample size was considered using the Epi Info™ StatCalc program [35] for unmatched or cross-sectional cohort studies. This minimum sample was estimated to provide greater than 80 % power to detect a 15 % difference in outcome on the primary outcome measure at the 95 % confidence interval using the Fleiss calculation. The acceptability of this power is supported by an emergent difference of 20 % in outcome HoNOS scores in a recent Australian study examining outcomes of a community residential service for similar consumers [36].

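### Excluding consumers discharged within six weeks of admission selects on an event that the staffing model may influence, and the plan has no analysis that would show the effect

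*Protocol article*

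**What the plan says.** All of this is in the Sample section of the protocol article. The cohort is every consenting consumer admitted to the three units in the study period, and "the only defined inclusion criteria is acceptance for a trial of CCU based rehabilitation care". The article then says "Each CCU provides a six-week assessment period to establish suitability for engagement under the model of service", and for that reason "consumers who are discharged prior to the conclusion of this assessment period will be excluded from the study". The stated purpose is to keep participants in line with the model of service.

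The resulting set is given a name: "This reflects a modified intention-to-treat approach". The justification is that "participants will be included regardless of their mode of exit from the CCU", with planned, unit-initiated and consumer-initiated exits listed as the modes.

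Progress to date is given for the three sites together: "50 of the 63 consumers admitted across all three sites met the inclusion criteria", and "42 (84.0 %) of eligible consumers provided consent to participate". Neither figure is split by staffing model.

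**The concern.** Eligibility begins at acceptance for a trial of care, but membership of the analysis set is settled up to six weeks later. By then the consumer has been living under the staffing model whose effect is being estimated. A unit can end the stay early, and so can the consumer. If the model affects either decision, the two retained groups have been filtered differently, and applying the same written rule at every site does not prevent that.

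The article itself supplies both links that such a bias needs. The Background regards better engagement through peer support as a promising possibility. The section on planned predictors uses mode of discharge as a proxy for engagement and hypothesises that consumers with a planned exit improve more. Early exit is thus plausibly related both to the exposure and to the outcome.

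The stake is the main conclusion. Under Aims and benefits, equivalent outcomes would support choosing staffing on secondary grounds such as cost and preference. A service making that choice admits everyone, including those who leave in the first weeks.

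**Working it through.** **1. The article's own figures (Sample).**
- Met criteria: 50/63 = 79.4%, as printed.
- Consented among eligible: 42/50 = 84.0%, as printed.
- Outside the criteria: 63 − 50 = 13, and 13/63 = 20.6%.
- Retained and consenting: 42/63 = 66.7% of admissions.

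Discharge before six weeks is the only exclusion the article defines, but it does not say that all 13 were early discharges. So 20.6% describes everyone outside the criteria and need not be the early-exit rate.

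**2. Order of events.** Acceptance and admission come first, then exposure to the unit's staffing, then the assessment, then exclusion or retention. Under Evaluation context, peer workers at the integrated sites take over non-senior nursing roles and carry out individual rehabilitation plans. The filter therefore acts after exposure has begun.

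**3. Whether the primary outcome requires the filter.** The primary outcome is the change in highest total HoNOS from the 12 months before admission to the 12 months after discharge, taken from administrative data (Sample; Primary outcome measure). Neither window depends on length of stay. HoNOS is recorded only at service contacts (Table 2, footnote A), so some early leavers may have no follow-up score.

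**4. Size of a possible bias.** For one model let e be the share excluded, R the mean of those retained, D the amount by which the excluded do worse (in SD), and M the mean of all admissions. Then

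M = (1 − e)R + e(R − D) = R − eD, so R = M + eD.

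For models A and B:

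retained difference = true difference + (e_A·D_A − e_B·D_B).

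The bracket is the bias. The article gives neither e by model nor D, so every row below is an assumption.

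| Assumed early exit | Assumed deficit D | Bias (SD) |
|---|---|---|
| 20.6% in both | same in both | 0 |
| 25% v 15% | 0.5 to 1.0 | 0.10 × 0.5 = 0.05 to 0.10 × 1.0 = 0.10 |
| 30% v 10% | 0.25 to 1.0 | 0.20 × 0.25 = 0.05 to 0.20 × 1.0 = 0.20 |
| 20.6% in both | differs by 0.5 to 1.0 between models | 0.206 × 0.5 = 0.10 to 0.206 × 1.0 = 0.21 |

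**5. Direction.** Take model A with 25% early exit, model B with 15%, and D = 1.0 in both. The bias is then +0.10 SD in favour of A.
- True difference 0: the retained groups differ by 0.10 SD, so a difference is created.
- True difference −0.10 SD: the retained groups differ by 0, so a difference is hidden.

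**6. Scale.** No equivalence margin is stated. At the planned minimum of 60 and 40 consumers, the standard error of a difference in means is √(1/60 + 1/40) = 0.204 SD. A bias of 0.05 to 0.10 SD is about a quarter to a half of that (0.05/0.204 = 0.25; 0.10/0.204 = 0.49).

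**The case against.** The rule is disclosed and reasoned. The assessment period exists to establish suitability, and comparing consumers found suitable is a legitimate question in a naturalistic cohort. All later exits are kept. The label already says modified. The Discussion acknowledges incomplete sampling and site differences in referral, and calls for attention to how participants and non-participants differ at each site. Allocation is not randomised and only one site has clinical staffing, so this adds to larger, acknowledged confounding. Extra tables and sensitivity analyses may also sit in an analysis plan that is not shown.

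Much of that stands. The six-week question is legitimate, and the size of the problem is unknown. What does not follow is that the rule is harmless. The Discussion presents the criterion only as aligning the sample with the model of service. The risk it names is the opposite one, that keeping non-completers may mask differences. A general comparison of participants with non-participants does not show whether early exit differed by staffing model. The exclusion and its label are fixed in this article, whatever a later plan adds.

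The rule also has a measurement side. In Table 2 the admission battery may be completed up to six weeks after admission and the discharge battery up to six weeks before discharge. For a stay shorter than six weeks both windows cover the whole stay, so admission-to-discharge change has little meaning. That supports the restriction for those secondary measures, but not for the primary outcome.

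**Conclusion.** The exclusion is a stated selection on a post-exposure event and can bias the comparison of staffing models. The documents do not show that it does: with no split by model, the bias could be zero. The 0.05 to 0.10 SD figure rests wholly on assumed early-exit rates of 15% v 25% and an assumed deficit of 0.5 to 1.0 SD. The wider assumptions tried reach about 0.2 SD.

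Four stronger readings are tempting and are not supported:
- **That the rule pushes the result toward equivalence.** That happens only if the model losing more poor-prognosis consumers is also truly the worse one, which nothing in the article indicates. With no true difference, unequal early exit with a similar deficit moves the retained groups apart.
- **That 20.6% of admissions were lost to early discharge.** The article does not give the reasons for the 13.
- **That peer workers decide who stays at the integrated sites.** The article does not say who judges suitability. The notes to Table 3 reserve the principal service provider role for clinical staff under both models.
- **That follow-up HoNOS exists for every early leaver.** It depends on later service contact, and the article expects missing administrative data.

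The label is a secondary matter. Inclusion whatever the mode of exit holds only after week six, so the name does not describe the set. Overall this is a gap that is cheap to close; it does not invalidate the study.

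**What to change.** 1. Report discharges before six weeks by site and by staffing model, with the reason and who initiated the exit. State how many of those outside the criteria were early discharges.
2. Pre-specify an analysis of the primary outcome (administrative HoNOS before admission and after discharge) in all consenting admissions regardless of length of stay, shown alongside the six-week set. Whether equivalence should have to hold in both sets is a debatable choice and is not part of this request.
3. State that the six-week set answers the question for consumers who complete assessment, and drop or qualify the modified intention-to-treat description.

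The cost is one administrative extraction for consenting early leavers and one further analysis. If all 63 admissions had been eligible and consented at the same 84%, about 63 × 0.84 = 53 would be analysed instead of 42. That is probably optimistic, because consent is reported only among the 50 eligible. Some early leavers will lack consent or a follow-up HoNOS, so coverage must be reported by model. The admission-to-discharge secondary measures cannot be extended to early leavers, because their two assessment windows overlap, and should stay with the six-week set.

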### Measures

#### Primary outcome measure

The primary outcome measure will be change in psychosocial functioning as measured by total score on the HoNOS [37]. It is hypothesised that there will be no significant difference in the mean change in highest total HoNOS score recorded in the 0–12 months prior to CCU commencement and the highest score recorded 0–12 months post CCU discharge for consumers under the clinical and integrated staffing model. The total HoNOS score has been selected as the primary outcome measure as it:Has high validity, reliability and sensitivity to change, as well as routinely informing service policy and planning decisions in Australia [38];Is considered appropriate for tracking changes in social functioning over time, and more sensitive in doing so than the CANSAS (a needs based measure) [39];Has an embedded role in individual outcome assessment in Australia and New Zealand [38, 40, 41] and there is evidence that it is being regularly utilised in care planning [42, 43]Is supported by an established national assessment protocol and training processes to facilitate inter-rater reliability [38], and with evidence to support higher levels of acceptability [44] and completion than the other core measures of routine outcome suite [38]It is used and available across multiple international settings [45], increasing the replicability of the methodology.

Utilising the criterion of the highest (i.e. greatest dysfunction) score in the 12-month period pre and post CCU entry limits the risk of conflating the benefits of active rehabilitation support with the benefits associated with support and accommodation in the CCU setting.

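### The power claim for 60 v 40 cannot be reproduced with the two-proportion method it names, and it is unsupported for the planned test of mean HoNOS change

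*Protocol article*

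**What the plan says.** The Sample section of the protocol article expects that "at least 60 consumers from the integrated staffing model and 40 from the clinical staffing model would agree to participate". The tool is then named: "The adequacy of the estimated minimum sample size was considered using the Epi Info", in its option for unmatched cohort or cross-sectional designs. The resulting claim is that these numbers are "estimated to provide greater than 80 % power to detect a 15 % difference in outcome on the primary outcome measure". The formula is given as Fleiss's and the confidence level as 95%. The support offered is: "The acceptability of this power is supported by an emergent difference of 20 % in outcome HoNOS scores in a recent Australian study".

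Three other places bear on this claim:
- **Primary outcome measure** predicts "no significant difference in the mean change in highest total HoNOS score" between the staffing models. The outcome is a score, and no responder definition is given for it.
- **Analysis** (quantitative) plans a t-test or Mann–Whitney U test for this comparison, at the 0.05 level.
- **Aims and benefits** commits the study to testing equivalence rather than superiority or non-inferiority.

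**The concern.** The method named for the power calculation does not fit the outcome or the test. Fleiss's formula takes two event rates, and the study will compare two means. The power figure therefore has to be checked on each reading of the 15%: as a difference in proportions, which the formula assumes, and as a fraction of a mean score, which the outcome implies.

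What is at stake is how a null result will be read. The study predicts no significant difference, and the aims say that equivalent care would allow staffing to be decided on secondary grounds such as cost-effectiveness. A reader who trusts more than 80% power for a 15% difference could take p > 0.05 as good evidence against a gap of that size. If the figure has no basis, neither has that reading.

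**Working it through.** **Inputs.** Clinical n = 40, integrated n = 60, difference 15%, 95% confidence (all from Sample); α = 0.05 (Analysis). Sidedness is not stated, so two-sided is assumed. No reference proportion, mean or SD is given.

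**1. The plan's own figure by its own method.** With p_c and p_i the clinical and integrated proportions and p̄ = (40p_c + 60p_i)/100, the Fleiss power is

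Φ{ [ |p_c − p_i| − 1.96·√(p̄(1−p̄)(1/40+1/60)) ] / √(p_c(1−p_c)/40 + p_i(1−p_i)/60) }.

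Example, 50% v 65%: p̄ = 0.59. The two standard errors are 0.1004 (null) and 0.1002 (alternative). (0.15 − 1.96 × 0.1004)/0.1002 = −0.47, so power is 32%.

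| Lower v higher rate | Clinical arm lower | Clinical arm higher |
|---|---|---|
| 5% v 20% | 57% | 64% |
| 10% v 25% | 46% | 52% |
| 20% v 35% | 36% | 39% |
| 30% v 45% | 32% | 34% |
| 40% v 55% | 31% | 31% |
| 50% v 65% | 32% | 31% |

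The stated figure appears only at the edge. Clinical 15% v integrated 0% gives 83.5% (the mirror case is 85% v 100%), and clinical 16% v integrated 1% already gives 79%. The limit is an integrated proportion within about 0.8 points of 0 or 100%. Clinical 0% v integrated 15% gives 78%. With the continuity correction (subtract (1/40 + 1/60)/2 = 0.021 from the difference) the two-sided maximum is about 73%.

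Other variants do not help:
- One-sided, power is about 43% at mid-range.
- With 15% read as relative, power is about 11% at a rate of 50%, and 25–28% at 80%.

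At 1.5:1 allocation, 80% power would need 65 + 98 = 163 participants at 5% v 20%, and 141 + 212 = 353 at 50% v 65%.

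**2. The outcome actually planned.** For two means, the standard error of the difference is SD × √(1/40 + 1/60) = 0.204 SD. The difference detectable with 80% power is (1.960 + 0.842) × 0.204 = 0.572 SD by the normal approximation, or 0.578 SD by the t distribution with 98 degrees of freedom.

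If 15% means 15% of a reference mean score, the standardised difference is 0.15 divided by (SD/mean). It reaches 0.578 when SD/mean = 0.15/0.578 = 0.26. The SDs below are assumed, because the article gives none.

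| SD of change, % of reference mean | Standardised difference | t-test power |
|---|---|---|
| 20 | 0.75 | 95% |
| 25 | 0.60 | 83% |
| 30 | 0.50 | 68% |
| 40 | 0.375 | 44% |
| 50 | 0.30 | 31% |

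**3. The stated aim.** No equivalence margin enters the calculation. For two one-sided tests at 5% and a true difference of zero, power is about 2Φ(margin/0.204 − 1.645) − 1, with margin in SD units. Setting this to 80% gives a margin of (1.645 + 1.282) × 0.204 = 0.60 SD. With t quantiles, power is 57% at a margin of 0.5 SD and 0.2% at 0.3 SD. The 90% confidence interval half-width is 1.661 × 0.204 = 0.34 SD.

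**The case against.** Four points can be made for the plan.

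- **Sixty v 40 is a floor.** The article calls it a likely under-estimate, and throughput rather than the calculation sets the sample. True, but the claim is made for this minimum sample, and the mid-range rates would need about 353.
- **A journal article condenses.** An SD or event rate may stand in a fuller document, so its absence is not counted here as a fault. The mismatch between formula and outcome is visible without it.
- **Power for the planned test might exceed 80%.** This stands. A reader might infer from the first table that the study has only 31–57% power. The documents do not support that: those figures belong to a two-proportion test that the study will not run. Power for the t-test cannot be determined from the article, and the favourable SDs in the second table are as possible as the unfavourable ones.
- **The 20% figure gives context.** A reader might go further and infer that 20% was the whole benefit of the cited service, so that a 15% gap would be most of it. The article does not say whether the 20% is a change over time or a difference between groups, so that argument cannot be made. What is visible is that the 20% is described as a difference in scores. It therefore does not support a power calculation for proportions.

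It is also fair to say that the absence of an equivalence margin and test is a wider matter than this sentence. It enters here only because power to detect a difference is offered in a study whose stated aim is equivalence.

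**Conclusion.** Wrong as written. The method named does not return more than 80% for any ordinary pair of proportions 15 points apart (two-sided 5%, no continuity correction, 40 v 60), and with the correction it never does. For the planned comparison of means the claim is unsupported rather than disproved: it holds if the SD of change is at most about 26% of the reference mean, and the article gives no basis for that. On either reading, the figure is not power to show equivalence. These conclusions rest on a two-sided 5% level, full follow-up of 60 and 40, roughly normal changes with equal SDs and, for the equivalence figures, a true difference of zero.

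**What to change.** Delete the Fleiss statement from the Sample section and state what 60 v 40 delivers for the continuous outcome:
- a detectable difference of about 0.58 SD (80% power, two-sided 5%);
- a 90% confidence interval half-width of about 0.34 SD;
- for the equivalence aim, 80% power by two one-sided tests only for a margin of about 0.60 SD, if the true difference is zero.

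Convert these to HoNOS points with the SD of change from the service's routine data; Table 2 of the article shows that HoNOS is already collected routinely. Do not cite the 20% score difference as support for a calculation on proportions.

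The cost is one paragraph and a less favourable statement of precision. Recruitment does not change and no extra participants are needed.

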## Background

Community based residential rehabilitation for mental health consumers in Australia has become increasingly available through non-government organisations (NGOs) and public health services [1]. These are bed-based services that focus on improving the independence and community functioning of persons affected by severe and persisting mental illness, predominantly those with a diagnosis of schizophrenia. The growth in availability of residential rehabilitation over the past 20 years has been linked in part to the recovery movement and research evidence promoting a more optimistic view of the potential for improvement among people with severe mental illness than has been previously assumed [2–4]. This paradigm shift has impacted the landscape of mental health policy and practice [5], facilitating a more holistic approach to treatment planning, and increasing the focus on addressing consumers’ functioning and attainment of personal goals [6]. However, at this time, there is limited evidence to guide service users, service providers and funding bodies about the effectiveness of residential rehabilitation service models [2] and how they should function.

There is limited research examining the outcomes of clinically focused community residential mental health rehabilitation services in Australia; much of what is available focuses on the consumers following their deinstitutionalisation [7]. With regards to non-clinical services, a 2012 consultation paper commissioned by the state of Victoria recommended discontinuation of bed-based adult rehabilitation services due to a lack of evidence of consumer outcomes and recovery oriented care [8]. Despite limitations in the evidence base, there has been substantial recent investment in additional capacity by the Queensland Government, with six new clinically operated community residential mental health rehabilitation services (126 beds) expected to open over the 2015–2016 period [9]. Novel approaches to the inclusion of peer workers have been considered for these units. There is a paucity of research to guide policy-makers, service providers and users as to the differences between models of staffing of residential mental health rehabilitation with regards to consumer preferences and outcomes. Better evidence about the effectiveness of these services, as well as the implications of integrating peer support workers into staffing models, is clearly needed.

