Another important aspect of mental health policy and practice linked to the recovery movement is the increasing emphasis on the availability of peer support [10–12]. The concept of peer support has been formalised in roles such as ‘peer workers’ or ‘peer support workers’ where an individual with a lived experience of mental illness is employed with the expectation these experiences will be explicitly utilised in supporting consumers of the service [13]. It is argued that this lived experience facilitates the sharing of experiential knowledge about coping strategies and pathways to recovery. Peer support roles are being increasingly encouraged and trialled as a component of mental health service provision. However, despite this strong policy backing, available evidence regarding the effectiveness of peer support has been criticised with regards to methodological rigor and potential bias [10, 13]. Much of the evidence relating to the value of peer support is qualitative in nature, and quantitative studies have been completed in outpatient and inpatient settings rather than community residential services. Notwithstanding these limitations, the literature suggests that peer workers employed as case managers achieve equivalent outcomes for service users in comparison with professional case managers, with potential advantages in terms of consumer engagement and benefits for peer workers and the services they work with [12–15]. The possibility of improved engagement through the inclusion of peer-support is promising, particularly given increasing interest in the impact of consumer engagement on rehabilitation outcomes [16, 17].

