### Analysis

The quantitative analysis will be undertaken in SPSS Version 22 and statistical significance will be assessed at a level of 0.05:The cohort of consumers utilising the services across the three sites will be defined using descriptive statistics. Differences between the sites and staffing models will be examined using t-tests and chi-squared analyses. Assuming comparability of the cohorts is established it is planned that the data from the two integrated staffing model sites will be able to be combined.In order to answer the question of equivalence of the integrated and clinical staffing model for CCUs, differences in the total HoNOS score pre admission and post discharge will be assessed using a t-test or Mann–Whitney U test depending on the normality of the distribution.The question of whether CCU rehabilitation care results in change in specific clinically relevant outcome domains, will be answered through analysis of the secondary outcome measures. It is anticipated that data from the secondary outcome measures will be dichotomised and subjected to Mann–Whitney U analysis with appropriate correction for multiple comparisons.Predictors of change in psychosocial functioning following CCU care will be explored using hierarchical linear regression modelling. The dependent variable is the same as the primary outcome variable for the overall study, mean change in total HoNOS score pre admission and post discharge from CCU care. The independent variables will be entered cumulatively with the organisational (Level 3) variable considered first, followed by the site related (Level 2) variables and then the consumer (Level 1) variables. A hierarchical approach is appropriate given the expectation of inter-correlation between the predictors [68].

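### The sample size is called acceptable because of a 20 % HoNOS difference whose comparison is not stated, and power to detect a 15 % difference is not power to conclude equivalence

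*Protocol article*

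**What the plan says.** The Sample section of the protocol article expects that "at least 60 consumers from the integrated staffing model and 40 from the clinical staffing model would agree to participate", a figure derived from service throughput, length of stay and a 70 % response rate. It checks adequacy with an Epi Info routine "for unmatched or cross-sectional cohort studies" and the Fleiss calculation. The minimum sample is said to give more than 80 % "power to detect a 15 % difference in outcome on the primary outcome measure at the 95 % confidence interval". The section then calls this power acceptable because a difference of 20 % was seen "in outcome HoNOS scores in a recent Australian study examining outcomes of a community residential service for similar consumers".

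The question the study asks is set elsewhere. Aims and benefits chooses equivalence testing over superiority or non-inferiority. Under Primary outcome measure: "It is hypothesised that there will be no significant difference in the mean change in highest total HoNOS score", compared between the clinical and integrated models. The quantitative Analysis section answers the equivalence question with a t-test or Mann–Whitney U test, and "statistical significance will be assessed at a level of 0.05".

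On earlier evidence, the Background states (the sentence is cut short here): "There is a paucity of research to guide policy-makers, service providers and users as to the differences between models of staffing of residential mental health". Of peer support it says that "quantitative studies have been completed in outpatient and inpatient settings rather than community residential services".

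**The concern.** The sentence on the 20 % is the only reason given for regarding the power as acceptable. It has two weaknesses.

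First, its relevance is not shown. The source is described only as a study of the outcomes of a residential service. The reader cannot tell whether the 20 % is a change over time, a gap between groups or something else. The primary comparison is between two staffing models that are meant to deliver the same model of service.

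Second, the logic does not fit the aim. A large difference seen elsewhere can reassure a reader that a study looking for a difference will find one. An equivalence conclusion needs the opposite assurance: that differences too large to ignore can be excluded.

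Aims and benefits says that a finding of equivalence would let staffing decisions turn on cost-effectiveness and consumer preference. If a non-significant test is read as equivalence, and the sample has been declared adequate on this basis, services could act on a reassurance that the data do not give.

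**Working it through.** **Inputs from the protocol article**
- Groups: 60 integrated, 40 clinical (Sample).
- Power: more than 80 % for a 15 % difference (Sample).
- Significance level: 0.05 (Analysis); two-sided is assumed here.
- Benchmark: 20 %, comparison not stated (Sample).
- Aim: equivalence (Aims and benefits); no difference hypothesised (Primary outcome measure).

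**Step 1. The plan's own figure.** It cannot be reproduced, because the article gives neither a baseline proportion nor a standard deviation and does not say what the 15 % is a percentage of. If 15 % means percentage points between two proportions (the setting of the Fleiss method), two-sided power at 40 versus 60 without continuity correction is:

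| Proportions | Power |
|---|---|
| 42.5 % vs 57.5 % | 31 % |
| 20 % vs 35 % | 36–39 % |
| 10 % vs 25 % | 46–52 % |
| 5 % vs 20 % | 57–64 % |

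Ranges reflect which group has the higher proportion. Worked for the first row, with the lower proportion in the clinical group: pooled proportion = (40 × 0.425 + 60 × 0.575)/100 = 0.515. SE under no difference = √[0.515 × 0.485 × (1/40 + 1/60)] = 0.1020. SE under the alternative = √[0.425 × 0.575 × (1/40 + 1/60)] = 0.1009. Power = Φ[(0.15 − 1.96 × 0.1020)/0.1009] = Φ(−0.495) = 31 %.

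If 15 % is a percentage of a mean, power depends on an unstated mean and standard deviation. The present point does not need the stated figure to be wrong, so the remaining steps take it as given.

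**Step 2. What the 20 % can support.** Set side by side:
- The benchmark is a 20 % difference in HoNOS scores in a study of a residential service. Which two values differ is not stated.
- The primary comparison is clinical versus integrated staffing, on the change from the worst score before admission to the worst score after discharge.
- The Background reports scarce research on differences between residential staffing models, and quantitative peer-support studies in other settings.

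Nothing in the article connects the first item to the second, and the third makes a connection unlikely without excluding it.

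**Step 3. Power to detect versus power to conclude equivalence.** Suppose power is exactly 80 % at a difference of 15. Then 15/SE = 1.96 + 0.842 = 2.802, so SE = 15/2.802 = 5.35 in the units of the 15 %. Assume also an equivalence margin of ±15 and a true difference of zero. The probability that the whole confidence interval lies inside the margin is

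2Φ(15/SE − z) − 1,

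with z = 1.645 for a 90 % interval (two one-sided tests at 5 %) and z = 1.96 for a 95 % interval.
- 90 % interval: 2Φ(2.802 − 1.645) − 1 = 2Φ(1.157) − 1 = 2 × 0.876 − 1 ≈ 75 %.
- 95 % interval: 2Φ(2.802 − 1.96) − 1 = 2Φ(0.842) − 1 = 2 × 0.80 − 1 = 60 %.

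**Step 4. Sensitivity, because the article says more than 80 %.**

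| Power at 15 % | 15/SE | 90 % interval | 95 % interval |
|---|---|---|---|
| 80 % | 1.96 + 0.842 = 2.802 | 75 % | 60 % |
| 85 % | 1.96 + 1.036 = 2.996 | 2Φ(1.351) − 1 = 82 % | 2Φ(1.036) − 1 = 70 % |
| 90 % | 1.96 + 1.282 = 3.242 | 2Φ(1.597) − 1 = 89 % | 2Φ(1.282) − 1 = 80 % |

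In each row the chance of concluding equivalence is below the power to detect. The 20 % enters none of these calculations.

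**The case against.** The best defence is that little turns on the sentence. The cohort is all consenting admissions from December 2014 to December 2017, so the size follows from throughput. Power was an adequacy check, and the 20 % a supporting remark. The 60 and 40 are called a minimum that is probably an under-estimate. Expecting no difference is compatible with asking what difference could be detected, and relating a tolerable difference to an effect seen earlier is ordinary reasoning in equivalence work. All of this stands as a limit on how much the point matters. It does not supply the missing link: the article neither says what the 20 % measures nor uses it to argue for a tolerable difference.

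Two stronger readings are tempting and should not be adopted.

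- A reader might infer that the article itself shows the 20 % is not a staffing contrast, or that it is a whole service's effect. It says neither. The Background reports scarcity of evidence, not absence, and its remark on peer-support studies does not describe the cited source.
- A reader might infer that 15 % is three quarters of the benchmark effect, and that a model losing half of it would usually go undetected. That needs both percentages on one scale, the 20 % to be the overall service effect, and exactly 80 % power. Power at 10 % is Φ(10/SE − 1.96). This is 46 % if power at 15 % is exactly 80 %, but 51.5 % if it is 85 % and 58 % if it is 90 %. The conclusion changes with an assumption the article does not fix.

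**Conclusion.** The point holds in limited form. The 20 % does not support the adequacy of the sample: what it compares is not stated, nothing ties it to clinical versus integrated staffing, and even a relevant larger difference would not show that equivalence can be concluded. The stated power answers a different question from the study's aim.

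On the illustrative assumptions (exactly 80 % power at 15 %, margin 15 %, true difference zero), the chance of concluding equivalence is about 75 % with a 90 % interval and 60 % with a 95 % interval. Higher power at 15 % raises both figures; a narrower margin or a non-zero true difference lowers them. The 15 % margin is an assumption of this illustration, not a figure from the article.

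This is a fault in the stated justification and in how a non-significant result would be read. It does not show that the study is too small.

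**What to change.** 1. In the Sample section, remove the 20 % difference as support for the sample size.
2. State there that the power figure is for detecting a 15 % difference and is not power to conclude equivalence. The 75 % and 60 % figures may be given as an illustration, with their three assumptions.
3. In the Analysis section, report the between-model difference in HoNOS change with its confidence interval, and base the equivalence conclusion on that interval, not on a non-significant t-test or Mann–Whitney test.

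Do not add a power figure for losing half of the 20 %, or a measure of the share of benefit retained. Both need the 20 % or the uncontrolled pre-to-post change to be read as the service's effect, which the article does not establish.

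The cost is a few sentences and one reported interval, with no extra participants. The stated adequacy becomes less favourable.
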